#### Analysis of secondary vocational and alcohol and drug-treatment-related outcomes

The ITT analysis of the secondary vocational and clinical outcomes will be done using appropriate mixed-effects regression models according to each measure (i.e. linear for time-based (total time in employment and treatment); Poisson for count-based (number of appointments; days of alcohol and drug use; number of treatment episodes); logistic for binary outcomes (sustained employment; *DSM-5 remission*); ordinal for treatment exit status; and proportional-hazards (for time to first employment) with measure-appropriate covariates. These models will include site and employment history stratification factors and may include other background variables. Exploratory models will also be separately done for AUD, OUD and other drug use disorder groups. A causal mediation framework analysis will be used to determine the evidence for a theoretical mechanism of change for the IPS intervention using the JSSE-B as a mediator of competitive employment.

After completing the analysis and reporting of the primary and secondary analyses, we plan to undertake exploratory longer-term analyses using the national registry data at 3 years and 6 years – subject to approval for a protocol amendment.

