#### Alcohol and drug dependence treatment-related

For the secondary outcomes and economic analyses, the following alcohol and drug dependence treatment-related outcomes will be included:
Alcohol consumption, drug use, drug injectingDSM-5 AUD, OUD and other drug use disorder remission statusTotal time enrolled in alcohol and drug use disorder treatmentNumber of AUD, OUD and other drug use disorder treatment episodesTreatment status at end of follow-up (enrolled, left successfully, left unsuccessfully, deceased)

Alcohol and drug use (recall: past 28 days) will be self-reported to site clinicians using the Treatment Outcomes Profile (TOP) [23]. The TOP is the English national outcomes monitoring instrument for publicly funded treatment services for drug and alcohol dependence. TOP data is uploaded to the National Drug Treatment Monitoring System (NDTMS). The TOP uses a structured, calendar-prompt, ‘timeline follow-back’ procedure [24] to maximise accuracy of drug and alcohol use reporting. The TOP will be administered by site clinicians as a structured personal interview at baseline, 6 months, 12 months,18 months and exit.

DSM-5 remission status will be assessed by personal interview by site clinicians at baseline, 6 months, 12 months and 18 months using the Structured Clinical Interview for DSM-5 (clinician version; SCID-5-CV) [25]. This has a checklist of 11 symptoms (each coded ‘present’ or ‘absent’) to diagnose disorder presence and severity (no symptoms = disorder not present; 1–3 symptoms = mild; 4–5 symptoms = moderate; ≥ 6 symptoms = severe). We will use the American Psychiatric Association’s definition for AUD and OUD remission (i.e. zero criteria except craving and using the ‘on maintenance therapy’ specifier as appropriate and not including tolerance and withdrawal item if the patient is adherent to their prescription).

NDTMS records will be used to determine each participant’s total time in treatment in the community and in prison, as well as the number of treatment episodes and status at the end of follow-up. For data modelling, we will record TOP and treatment exposure data for 18 months prior to randomisation for those members of the cohort with a history of prior treatment for alcohol and drug dependence.

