#### Primary vocational effectiveness

The statistical analysis plan (SAP) will be approved by the trial committees and will be published on the Open Science Framework (OSF; www.osf.io) before it is implemented after data-lock. There will be no interim analyses and specified trial-stopping rules. The analysis of the primary outcome (completed in STATA or R; final code to be placed on OSF) will follow the intention-to-treat (ITT) principle and include all patients in the group to which they are allocated. Alpha will be set at 5% for the primary and secondary outcomes (with associated 95% CIs). The distributions of scale and count measures may be non-normal (skewed), so that test statistics and effect sizes may be computed following appropriate transformation (e.g. natural log to obtain a geometric mean).

Data from all sites will be pooled and the superiority effectiveness estimate for the IPS intervention (adjusted OR and CI) will be determined using a mixed-effects, multi-variable logistic regression model. The model will include the stratification variables and a random intercept for each site to account for clustering. A maximum-likelihood multiple-imputation approach will be used for the management of missing data with a sensitivity comparison to the complete case dataset.

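### Poisson regression with no stated dispersion allowance makes intervals for 28-day use much too narrow, for job counts somewhat too narrow, and for treatment episodes probably too wide

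*Protocol article*

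**What the plan says.** In the protocol article's section on the analysis of secondary vocational and treatment-related outcomes, the intention-to-treat analysis "will be done using appropriate mixed-effects regression models according to each measure". An i.e. then introduces a list of families. For counts the list gives "Poisson for count-based (number of appointments; days of alcohol and drug use; number of treatment episodes"; for durations, "linear for time-based (total time in employment and treatment". The section provides for covariates. It names no dispersion parameter, robust standard error or alternative count family.

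The section on treatment-related outcomes defines the measure of use: "Alcohol and drug use (recall: past 28 days) will be self-reported to site clinicians". The interviews take place at baseline, 6, 12 and 18 months and at exit.

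Three statements in the section on primary vocational effectiveness also bear on the point:
- On error rates: "Alpha will be set at 5% for the primary and secondary outcomes (with associated 95% CIs".
- On random effects, for the primary model: "a random intercept for each site to account for clustering".
- On skewed scale and count measures: "test statistics and effect sizes may be computed following appropriate transformation (e.g. natural log to obtain a geometric mean".

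**The concern.** A Poisson model takes its standard errors from the assumption that variance equals mean. If the true variance is larger, intervals are too short and the test rejects too often; if smaller, the reverse. A site intercept absorbs differences between sites, not differences between people within a site.

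Days of use in a 28-day window is a bounded measure, and in a treated population it may well gather at abstinence and at daily use. That is far from Poisson. At stake is a spurious finding that IPS changed alcohol or drug use, reported at a nominal 5% with a 95% interval that does not have that coverage.

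A related caution concerns the log option. Total time in employment is zero for everyone who finds no work, and zero has no logarithm.

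**Working it through.** **Inputs from the protocol article.** Competitive employment 0.36 (IPS) and 0.18 (TAU); 1:1 allocation; two-sided 5%; minimum sample 832; seven sites; recall window 28 days.

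**The plan's own figures.** The article gives no figure for the Poisson or log analyses. Its sample size, from which the employment rates are taken, reproduces. Comparing 0.36 with 0.18 needs 126 per arm at 90% power, and 252 × 1.2 = 302.4 (stated 302). At 80% power it needs 95 per arm, and 190 × 1.2 = 228 (stated 228). The total is 302 + 302 + 228 = 832.

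**Formulas.** Let φ = variance / mean. The Poisson standard error is 1/√φ times the correct one. The true error rate of a nominal 5% test is 2 × [1 − Φ(1.96/√φ)]. It depends on φ and not on sample size, so recruiting beyond 832 does not help.

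**Days of use, no pile-up assumed.** For an even spread over 0 to 28, the mean is 14, the variance is (29² − 1)/12 = 70, and φ = 70/14 = 5. The standard error ratio is 1/√5 = 0.45. The error rate is 2 × [1 − Φ(1.96/2.236)] = 38%.

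**All three counts under assumed distributions.** The article gives no distributions. For days of use, each row fixes the shares at 0 and 28 and spreads the rest evenly over 1 to 27. For jobs, the 73% with none is (0.64 + 0.82)/2 from the planning rates; the split among workers is assumed. The split of episodes is assumed. The simulated rates come from 1,000 null trials of 832 participants, with site as a fixed effect in place of a random intercept.

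| Outcome | Assumption | φ | Rate by formula | Simulated rate, Poisson SE | Simulated rate, robust SE |
|---|---|---|---|---|---|
| Days of use | 40% at 0, 5% at 28 | 10.7 | 55% | 55.7% | 4.9% |
| Days of use | 50% at 0, 20% at 28 | 14.1 | 60% | 61.2% | 5.6% |
| Days of use | 70% at 0, 10% at 28 | 17.6 | 64% | 64.1% | 6.0% |
| Job appointments | workers hold 1/2/3/4 jobs: 75/18/5/2% | 1.3 | 9% | 8.2% | 4.9% |
| Job appointments | workers hold 1/2/3/4 jobs: 50/25/15/10% | 1.9 | 16% | 15.9% | 4.8% |
| Treatment episodes | 1/2/3 episodes: 70/22/8% | 0.29 | about 0% | 0.0% | 5.5% |

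For days of use the Poisson standard error was 0.24 to 0.31 of the robust one, for jobs 0.73 to 0.88, and for episodes 1.9 times it.

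**Log option for employment time.** With 416 per arm, non-workers number 416 × 0.64 = 266 (IPS) and 416 × 0.82 = 341 (TAU). Together that is 607 of 832, or 73%. A plain log is defined only for the other 150 and 75, or 225 participants. In 1,000 simulated trials where workers' time had the same assumed log-normal distribution in both arms, so that all benefit lay in more people working:
- log time among workers rejected in 5% of runs;
- a comparison of mean time in all participants rejected in 91%;
- log(time + 1) in all participants rejected in 100%.

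**The case against.** The article promises appropriate mixed-effects models, and only the primary model's random effect is described. Use is measured repeatedly, so a participant random effect is possible and would absorb part of the excess variance; covariates would absorb some too. Dispersion checks can properly sit in the SAP, which is not shown. The distributions above are assumed. All of this stands, and it makes the size conditional. It does not remove the point, because the article names the Poisson family itself in a closed list. Nor does the result need extreme assumptions: a dispersion of only 2 still gives about 17%.

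A reader might infer that every count outcome would show false significance. The documents do not support that. Job counts are moderately affected. Participants must already be in treatment to enter, so most plausibly have at least one episode, and Poisson intervals would then be too wide.

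A reader might also infer that the plan drops non-workers from an intention-to-treat analysis and so deprives the economic analysis of an arithmetic mean. It does not say so. Total time in employment is given a linear model under intention-to-treat, which keeps the zeros. The log is an optional example, and log(time + 1) would keep everyone. The economic analysis has its own plan, and its description mentions no log. What remains is the caution that a plain log cannot be used where about 73% of values are zero.

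**Conclusion.** The point holds in this limited form. For days of alcohol and drug use, Poisson regression without a participant-level or dispersion term gives intervals much too narrow. The false-positive rate is about 38% for an even spread over 0 to 28, and about 55% to 64% with the assumed pile-up at 0 and 28. For number of job appointments it is about 8% to 16%, resting on the planning rates and an assumed 1 to 4 jobs per worker. For treatment episodes Poisson is probably conservative, on an assumed split.

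The 28-day bound and the 73% zero share come from the document; the rest of each distribution does not. The participants' own baseline interviews would show the actual dispersion.

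Only secondary outcomes are affected. The primary logistic analysis and the 832 are not, so this is a worthwhile correction and not one on which the trial's main conclusion depends.

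**What to change.** 1. State robust (sandwich) standard errors for all Poisson models. They correct the error in either direction. Negative binomial regression would not do this for treatment episodes, because it cannot represent a variance below the mean. Compute the sandwich at participant level, since seven sites are too few to serve as clusters.
2. For 0 to 28 days of use, specify a beta-binomial, an ordinal or a robust-error mean model. If the repeated interviews are modelled jointly, state the participant-level term.
3. For total time in employment, and for job tenure if it is analysed the same way, keep the linear intention-to-treat model on all participants, zeros included, with robust or bootstrap intervals. State that the optional natural-log transformation does not apply to these outcomes.

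The cost is a few sentences in the SAP and a few lines of code, settled before data-lock. The price is wider intervals for days of use and job counts.

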### Procedure

All keyworkers and ES will complete National Institute for Health Research’s Good Clinical Practice (GCP) training. Potential participants will be referred to an ES in the clinical team to discuss the study. The King’s College London Clinical Trials Unit will programme and independently manage the study randomisation system on a secure website. Immediately after securing informed consent (IPS-AD Participant Information Sheet (PIS) and Participant Consent Form (PCF) is available from the corresponding author on request) and completion of baseline study questionnaires, the ES will access the randomisation website to assign the participant to the intervention or control condition. Group allocation (ratio 1:1) will be done using block randomisation (with varying block size) stratified by site, clinical diagnosis (AUD, OUD, other drug use disorder) and work history (1 month or less versus more than 1 month of paid employment in the last 5 years).

The randomisation system will immediately confirm the participant’s allocation to IPS or TAU by email. The ES will then inform the participant and their keyworker. Participants assigned to TAU will be given an information pack containing details of standard employment support services available locally and will have no further contact with the ES. It will not be feasible to blind clinicians to trial condition allocation. Enrolment in TAU will be ongoing after the trial according to patient preference and local policy.

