### Sample size

Following preliminary planning, we followed the DELTA^2^ guideline to estimate the minimum sample size for the study [27]. Frederick and VanderWeele’s meta-analysis [7] was used to specify the important and realistic target difference for the primary outcome, with an estimate of its uncertainty. A sensitivity calculation was included if assumptions are mis-specified.

For comparison to the duration of the IPS intervention in IPS-AD, we used the rate of competitive employment status reported by seven superiority trials which evaluated 12 months of IPS (928 participants; outcome rate 0.36 for IPS and 0.13 for TAU; odds ratio (OR) 3.76; 95% CI 2.70 to 5.24). Conservatively, we used the lower bound of the CI (i.e. 2.70; equivalent to an outcome rate of IPS 0.36 and TAU 0.18).

To achieve 90% power to detect this 18% target difference (with a two-sided 5% level of statistical significance and a 20% increase to compensate for missing or inaccurate NINO information) we estimate that 302 participants will be required with AUD and OUD (giving an expected 95% CI estimate for the OR effect within a range from 1.50 to 4.36). If the observed effect falls short of the target difference, we will be able to detect a 15% difference (which we judge is still important) with 83% power (OR 95%, CI 1.24–3.46).

Given the lower number of people in treatment with other drug use disorders, we expect to recruit fewer participants in this group, so it will be realistic to power the analysis at 80%. For the 18% target difference (two-sided, 5% level of significance and with 20% increase for attrition), 228 participants will be needed (95% CI 1.35–4.57).

For the secondary outcome of total time worked, four of the seven trials used for the power calculation for the primary outcome measure in the meta-analysis reported the total number of hours worked (i.e. the sum of all time in all competitive employment during the trial). These four trials recruited 376 participants and the pooled mean difference was 505 h (Hedges’ *g* effect size = 0.54; 95% CI 0.33–0.74). Using this effect size as the realistic mean target difference, the analysis of the secondary outcome for length of competitive employment will have 99% to detect this target difference for the AUD and OUD groups. For the other drug use disorder group, we will be able to detect an effect size ranging from 0.54 to 0.38 with a minimum of 82% power.

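### The secondary-outcome models are committed to only two of the three stratification factors; clinical diagnosis is left optional

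*Protocol article*

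**What the plan says.** Three places in the Protocol article bear on this.

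- **Procedure.** Allocation is 1:1 in blocks of varying size, "stratified by site, clinical diagnosis (AUD, OUD, other drug use disorder) and work history". That makes three factors.
- **Primary vocational effectiveness.** "The model will include the stratification variables and a random intercept for each site to account for clustering". Diagnosis is a stratification variable, so it is in the primary model.
- **Analysis of secondary vocational and alcohol and drug-treatment-related outcomes.** The mixed-effects models are fitted "with measure-appropriate covariates", followed by: "These models will include site and employment history stratification factors and may include other background variables". Two of the three factors are named as certain. Diagnosis reappears only here: "Exploratory models will also be separately done for AUD, OUD and other drug use disorder groups".

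The primary section also sets a 5% alpha for both primary and secondary outcomes.

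**The concern.** A factor that constrains the randomisation should normally be in the analysis. Stratifying forces the arms to be nearly balanced on diagnosis, so the true sampling variance of the treatment effect no longer contains the between-diagnosis component. A model without diagnosis leaves that component in its residual variance and reports standard errors that are too large.

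The secondary list covers days of alcohol and drug use, remission status, time in treatment, number of treatment episodes and exit status. These are outcomes for which the type of substance disorder could plausibly matter a good deal. It also covers sustained employment (logistic) and time to first employment (proportional hazards). For those two, leaving out a prognostic factor changes the quantity being estimated, generally towards the null. Their ratios would then not be conditional on diagnosis, whereas the primary odds ratio is.

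**Working it through.** **1. The article's own sample-size figures.** These are not disputed; they supply the diagnosis split used below. Inputs from Sample size: "equivalent to an outcome rate of IPS 0.36 and TAU 0.18", two-sided 5%, 90% power for AUD and for OUD, 80% for other drug use disorder, and a 20% increase. With pooled variance under the null and no continuity correction,

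n per arm = [1.96·√(2·0.27·0.73) + z·√(0.36·0.64 + 0.18·0.82)]² / 0.18²

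- 90% power (z = 1.2816): 126 per arm, 252 in total, ×1.2 = 302.4 (stated: 302).
- 80% power (z = 0.8416): 95 per arm, 190 in total, ×1.2 = 228 (stated: 228).
- 302 + 302 + 228 = 832, the stated minimum.

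**2. Factors set side by side.**

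| Factor | Randomisation | Primary model | Secondary models |
|---|---|---|---|
| Site | yes | yes | will include |
| Work history | yes | yes | will include |
| Clinical diagnosis | yes | yes | optional at most |

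**3. Effect of omission, simulated.** The assumptions are ours, because the article gives no prognostic strength for diagnosis: 832 participants split 302/302/228; seven sites; blocks of 2, 4 or 6 within strata; a continuous outcome with residual SD 1; diagnosis effects of s × (1.0, −1.2, 0.3). Site (as fixed indicators) and work history are adjusted for throughout. There were 4,000 runs under the null and 2,000 with a 0.2 SD effect.

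Variance share of diagnosis: the weighted mean of (1.0, −1.2, 0.3) is 8/832 = 0.0096 and the weighted mean square is 757.4/832 = 0.9103, so the between-diagnosis variance is 0.910·s². The share of what remains after site and work history is 0.910s²/(1 + 0.910s²).

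| s | Share | Type I error without / with diagnosis | Power without / with diagnosis |
|---|---|---|---|
| 0 | 0% | 0.051 / 0.051 | 0.82 / 0.82 |
| 0.25 | 5% | 0.039 / 0.045 | 0.82 / 0.83 |
| 0.5 | 19% | 0.029 / 0.048 | 0.76 / 0.83 |
| 1.0 | 48% | 0.007 / 0.051 | 0.56 / 0.82 |

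**4. Check by formula.** With diagnosis balanced, the true standard error is about 2/√832 = 0.0693, and the reported one is larger by k = √(1 + 0.910s²). The test then rejects when |Z| > 1.96k, and power is Φ(0.2/0.0693 − 1.96k) = Φ(2.884 − 1.96k).

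- s = 0.25: k = 1.028, type I error 0.044, power 0.81.
- s = 0.5: k = 1.108, type I error 0.030, power 0.76.
- s = 1.0: k = 1.382, type I error 0.007, power 0.57.

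These agree with the simulation to within its error (standard error about 0.003 for type I error and 0.009 for power). The same k is the factor by which intervals are too wide: about 3%, 11% and 38%.

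**The case against.** **The wording does not exclude diagnosis, and the SAP can settle covariates.** The first part stands: both flexible phrases allow diagnosis in, so the fair statement is that the article does not commit to it. The second part does not dispose of the point. The article is not silent; it says which stratification factors the secondary models will contain, and the list is one short. An SAP that follows this text carries the gap forward, and one that adds diagnosis goes beyond it.

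**Diagnosis is handled by the separate models.** Those are exploratory and give estimates within each group. They do nothing for the precision of the pooled secondary estimates.

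**The consequences are mild.** Largely true. The error is in the conservative direction, the primary analysis is untouched, and large losses need a strongly prognostic diagnosis. The change in odds and hazard ratios is non-collapsibility and not confounding; it does not affect the linear or Poisson models in the same way.

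**Stronger readings that the document does not support.** A reader might infer that the primary model enters site twice, as a fixed effect and as a random intercept, leaving the intercept variance unidentifiable. No fixed site effect is stated. The ordinary reading is fixed terms for diagnosis and work history, with site entering through its random intercept.

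A reader might also take the Background unemployment rates (70%, 85% and 68%) as a measure of how prognostic diagnosis is. They describe everyone in community treatment, whereas the trial enrols only people out of work for at least six months who want a job. Even taken at face value, 30%, 15% and 32% not unemployed, weighted 302/302/228, give a mean of 0.251, a between-group variance of 0.0059 and a total variance of 0.188. The share is then 0.0059/0.188, about 3%, and intervals would be about 1.6% too wide (1/√(1 − 0.031) = 1.016).

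**Conclusion.** The inconsistency is real and is confined to the secondary outcomes: three factors in the randomisation and the primary model, two committed to in the secondary models. If diagnosis is in fact left out, the cost is precision and comparability, not validity. It is negligible where diagnosis barely predicts the outcome. It could be material for substance use, remission and treatment outcomes if diagnosis explains something like a fifth or more of the variance.

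That size is an assumption, since the article reports nothing from which to estimate it. The simulation is for a linear model and is only indicative for the Poisson, logistic, ordinal and hazards models. The point is worth correcting because the correction is free, not because any stated result is at risk.

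**What to change.** In the secondary-analysis section, replace the two-factor list with all stratification factors, named as site, clinical diagnosis (three levels) and work history (two levels). Keep the optional clause for genuinely additional background variables. Carry the same wording into the SAP.

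As an optional clarification in the primary section, say that diagnosis and work history are fixed effects and that site enters once, through the random intercept.

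The cost is a phrase in one sentence, or two with the clarification. Diagnosis is needed to randomise, so it is known for every participant. No data collection, sample-size figure or primary result changes.
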